### Adverse events

All potential adverse events will be recorded in the participant’s WBV diary (24). Mild to moderate adverse events that participants with PAD might experience as a result of WBV were identified from previous relevant studies (39–42), and include transient ones that resolve a few minutes after the WBV session (e.g., skin itchiness), although delayed onset muscle soreness (DOMS) due to the physical activity sessions will also be classified under this category (**Table 3**). Since WBV is a novel therapy for PAD, participants will be regularly monitored for the occurrence of any severe adverse events (**Table 3**), which could prematurely end the trial if likely associated with WBV. Adverse events will be assessed as objectively as possible and classified according to the Common Terminology Criteria for Adverse Events (CTCAE) v5.0 (39).

**Table 3 T3:** List of potential adverse events.

Severity	Adverse event
Mild/Moderate	Delayed-onset muscle soreness (DOMS)
	Dizziness
	Drowsiness
	Falls
	Leg tingling
	Mild (temporary) headache
	Mild (temporary) knee pain
	Muscle fatigue
	Skin itchiness or redness
Serious	Arterial thromboembolism-related life-threatening consequences (hemodynamic or neurologic instability)
	Arterial thromboembolism-related death
	Hypertensive emergency (≥180/110 mmHg) requiring urgent intervention
	Hypertensive emergency-related death

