The intervention will consist of 12 weeks of clinic-based supervised WBV on a Galileo Basic vibration plate (Novotec Medical, Pforzheim, Germany). All participants will be able to access subsidized transport to and from the clinic for the duration of the treatment period. The intervention protocol will be adapted from previously developed and implemented WBV protocols (24), with adjustments informed by previous studies investigating glycemic control and leg blood flow in individuals with T2D (19, 25). Participants will perform WBV three times per week for 12 weeks at a frequency ranging from 15 to 27 Hz and an amplitude of 2 to 4 mm (19, 25) (**Table 1**). Each training session will last approximately 22–28 minutes and will consist of 5-minute warm-up involving stretching exercises, three WBV bouts lasting 3–5 minutes each separated by 1-minute rest periods (resulting in a total WBV exposure of 12–18 minutes), and a 5-minute cool-down with stretching exercises. The vibration frequency, amplitude, and bout duration will be progressively adjusted throughout the intervention in accordance with the progression scheme described in **Table 1**. Participants will need to stand on the plate while barefoot, with knees slightly bent and a straight back posture (24). If needed, participants with poor balance may use a specifically designed adjustable metal frame for balance and support to ensure the patient can safely perform WBV (24). All sessions will be performed under the supervision of an experienced physiotherapist, part of the research team. A WBV diary will be maintained to record the patient’s progress, compliance with the study protocol, and any potential adverse events (including tiredness or pain) (24). Full adherence (100%) will be completion of all 36 sessions at the prescribed intensities and durations.

**Table 1 T1:** The 12-week whole-body vibration training (WBV) protocol.

Exercise components		Week											
		1	2	3	4	5	6	7	8	9	10	11	12
Warm-up		5-minute stretching											
WBV	Frequency (Hz)	15	18	20	22	24	27	27	27	27	27	27	27
	Amplitude (mm)	2	2	2	3	3	3	3	4	4	4	4	4
	Vibration bout (min)	3	3	3	4	4	4	4	5	5	5	5	5
	Set (*n*)	3											
	Rest periods (min)	1											
Cool down		5-minute stretching											

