The control group will attend supervised treadmill walking three times weekly for 12 weeks. The program will progressively increase in duration across the intervention period and will include stretching prior to and after each session. Walking speed and grade will be individually adjusted to reach the target intensity: participants with symptomatic PAD will walk until experiencing moderate claudication pain before resting and resuming, while those with asymptomatic PAD will walk continuously at a moderate intensity. In brief, both moderate intensities are assessed using subjective participant-reported measures. The moderate claudication pain in participants with symptomatic PAD is determined using a PAD-specific leg pain scale (26), a subjective pain intensity assessment tool. For individuals with asymptomatic PAD, moderate intensity is measured using the Borg Rating of Perceived Exertion (RPE) 6–20 scale (12, 13), a subjective exertion-based intensity measure, corresponding to moderate intensity as defined by the American College of Sports Medicine (ACSM) (27). The protocol was adapted according to Cochrane recommendations for standard walking therapy in PAD (11) (**Table 2**).

**Table 2 T2:** The 12-week treadmill walking training protocol.

Exercise components			Week					
			1–2	3–4	5–6	7–8	9–10	11–12
Warm-up			5–minute stretching					
Walking	Frequency (sessions/week)		3					
	Time (min)		15	20	23	25	27	30
	Intensity	Symptomatic PAD	• Start at 2.5–3.0 km/h, 0% grade • Adjusting speed (0.2–0.5 km/h) or grade (1–2%) to elicit a moderate claudication pain (3–4/5 claudication scale) within 3–10 min					
		Asymptomatic PAD	• Start at 2.5–3.0 km/h, 0% grade • Adjusting speed (0.2–0.5 km/h) or grade (1–2%) to maintain a moderate intensity (RPE 11–13)					
Cool-down			5–minute stretching					

PAD, peripheral arterial disease; RPE, rating of perceived exertion (Borg scale).

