### Data reporting and statistical analyses

Demographic and clinical characteristics of participants at baseline will be reported for each group. The effectiveness of WBV on the primary outcome (ISWT) will be assessed on the intention-to-treat principle using all data collected on randomized participants. Data will be analyzed using a general linear model, adjusted for the participant’s age, sex, PAD categories (symptomatic or asymptomatic), diabetes duration, and the distance covered in the ISWT at baseline. The effect size will be reported as the adjusted between-group difference and its 95% confidence interval (CI). The potential interactions between randomization group and sex will be tested, and sex-specific differences reported as appropriate.

The same model structure will be used to examine the potential effectiveness of the intervention on secondary outcomes. Per-protocol analyses may be also carried out on primary and secondary outcomes excluding recipients with major protocol violations, in particular, lower levels of adherence (defined as completion of <67% of prescribed sessions).

Data will be analyzed using SAS v9.4 (SAS Institute, Cary, NC, USA) and/or SPSS v31 (IBM Corp, Armonk, NY, USA). Missing data on the primary outcome will not be imputed. All statistical tests will be two-sided at p<0.05, with no adjustment for multiple comparisons (44). Trial findings will be reported according to CONSORT 2010 guidelines (45).

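### The only adverse-event and compliance record named is a diary described for the vibration arm, and Table 3's sorting by event type conflicts with CTCAE classification, so equal capture of harms is not secured and the trial-ending category is ambiguous

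*Protocol article*

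**What the plan says.** **Recording.** The Adverse events section sets a general rule: "All potential adverse events will be recorded in the participant’s WBV diary". The diary is introduced in the Study design section, in the paragraph on the vibration intervention before Table 1: "A WBV diary will be maintained to record the patient’s progress, compliance with the study protocol, and any potential adverse events". The paragraph on the comparator, before Table 2, opens with "The control group will attend supervised treadmill walking three times weekly for 12 weeks". It goes on to duration, speed, grade, claudication pain and perceived exertion, and names no diary, attendance log or event record.

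**Event list.** The Adverse events section explains where the milder events come from: "Mild to moderate adverse events that participants with PAD might experience as a result of WBV were identified from previous relevant studies". Table 3 is captioned "List of potential adverse events". Its first column is headed Severity and takes two values, Mild/Moderate and Serious.

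**Grading.** The same section adds: "Adverse events will be assessed as objectively as possible and classified according to the Common Terminology Criteria for Adverse Events (CTCAE) v5.0". It also says that participants are monitored for severe events, with a pointer to Table 3, and that such events could end the trial early if attributed to WBV.

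**Adherence.** The statistical analysis section allows a per-protocol analysis that excludes low adherence, "defined as completion of <67% of prescribed sessions". This rule is not limited to one arm.

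**The concern.** There are two linked problems.

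First, the rule on where events are recorded points to a form that the article describes for one arm only, and the list of milder events was drawn up for that same arm. The Blinding section says that neither participants nor assessors will be blinded. If staff follow the text literally, vibration participants have events noted in a diary kept for that purpose, while treadmill participants have them noted wherever and whenever someone thinks to do so. A difference in event counts could then reflect the recording as much as the treatments. The article calls WBV a novel therapy for peripheral arterial disease, so the safety comparison matters, and events not captured at the time of a session are hard to recover later. The same gap affects adherence, because compliance is a stated purpose of the diary.

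Second, Table 3 places event types in a severity category in advance, while the text says events are classified by CTCAE. The category that could stop the trial has one name in the text and another in the table. Two people applying the section to the same event could reach different answers.

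**Working it through.** The article gives no figure to reproduce on this point, so the check sets its passages side by side, with three small counts.

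**1. Which arm has a named record?**

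| Item | WBV arm | Treadmill arm |
|---|---|---|
| Supervised sessions | 3 per week × 12 weeks = 36 | 3 per week × 12 weeks = 36 |
| Named record of adverse events | WBV diary | none named |
| Named record of compliance | WBV diary | none named |
| Definition of full adherence | all 36 sessions at the prescribed intensities and durations | none given |
| Source of listed mild/moderate events | expected from WBV | not mentioned |

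Contact is equal at 36 supervised sessions per participant in each arm. The asymmetry lies in the record, not in the opportunity to observe.

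**2. What does the per-protocol rule need?** The threshold is 0.67 × 36 = 24.12 sessions. A participant with 24 sessions has 24/36 = 66.7% and counts as low adherence. One with 25 has 25/36 = 69.4% and does not. Membership of the per-protocol set can turn on a single session, so both arms need an exact count. Only the WBV arm has a named source for it.

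**3. How does Table 3 classify?**
- Mild/Moderate: 9 entries. Two of them (headache, knee pain) are themselves qualified as mild and temporary. Falls carries no qualifier.
- Serious: 4 entries, all thromboembolic or hypertensive, two of them deaths.
- Severe: 0 entries, although the text refers the reader to Table 3 for severe events.

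The text also places delayed-onset muscle soreness in the milder category by type, whatever its intensity, so the table is not used purely as an illustration.

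**4. Set against the CTCAE sentence.** Reading classification under CTCAE as grading each event on its own features (an assumption, since the article does not spell this out), a fall with injury could receive a higher grade than its row in Table 3 implies. The section does not say which of the two governs. Severity (how intense an event is) and seriousness (what its consequences are) also share one column, so the category that could end the trial is not uniquely defined.

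**The case against.** The strongest reply is that this is a condensed article, and a session log or case report form for the control arm is the sort of detail left to the full protocol. Several statements are not limited to one arm. The Abstract says adverse events will be monitored. The Adverse events section speaks of the participant's diary and of monitoring participants. Study data go into REDCap forms. The adherence rule presupposes attendance counts in both arms. Control sessions are supervised as often as vibration sessions. Table 3 is captioned as a list of potential events, and the CTCAE sentence stands beside it. Harms are not the primary outcome, the per-protocol analysis is optional, and early termination is discretionary.

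Much of this stands, and it rules out three stronger readings that a reader might infer:

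- *That control-arm events will go unrecorded, so harms cannot be compared between arms.* No passage says so, and the wording that is not arm-specific points the other way. What can be said is that equal capture is not specified.
- *That an injurious fall will be filed as mild or moderate.* The article does not mention injurious falls, and the CTCAE sentence could lead to a higher grade. The defect is two unreconciled rules, not a certain misclassification. Nor does the article say that the four serious entries are exhaustive.
- *That the bias can be given as a rate ratio.* This would need the fraction of events captured in each arm, which the documents do not give. Any ratio would simply restate an assumed fraction.

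The reply does not remove the point. The recording rule is a positive statement covering all adverse events, not a silence to be filled in elsewhere, and it names an arm-specific form. REDCap says where data are stored, not how control-arm events are elicited. The conflict between Table 3 and the CTCAE sentence lies within one section of the article.

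**Conclusion.** The point holds in a limited form. As written, the article does not secure equal ascertainment of harms, or of session completion for the per-protocol rule, in an open-label trial. Table 3 and the CTCAE sentence conflict, and the mismatch between severe and serious leaves the trial-ending category ambiguous.

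No numerical size can be attached. The direction of any bias is also open: a diary kept in one arm only would tend to make WBV look worse, but the difference depends on what is actually recorded in the treadmill arm, which the article does not state. The primary walking-distance analysis and the sample size are unaffected. What is at stake is the safety comparison, the per-protocol set and the clarity of the termination trigger.

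The conclusion assumes that the diary is used as the article describes it, and that no shared session form exists in a document not shown. If one does exist, the first part reduces to a correction of wording. The second part would still need reconciling.

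**What to change.** Before enrolment:

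1. Replace the WBV diary with one identical session record for both arms, covering attendance, dose completed and the same adverse-event questions at every supervised session. Correct the Adverse events and Study design sections to refer to it.
2. Tabulate adverse events and session completion by arm.
3. Reconcile Table 3 with the CTCAE sentence: keep the table as a list of anticipated events, grade each event individually, and record severity and seriousness as separate items.
4. Reconcile severe and serious so that one defined term names the category that triggers review of the trial. Which events belong in that category is for the investigators to settle.

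The cost is a revised form, a few sentences of text and a few minutes of form completion per session. Both arms already attend three supervised sessions a week, so no visits are added.

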### Blinding

Due to the nature of the intervention, it is not possible to blind participants to the treatment protocol they will be performing. In addition, it would be logistically challenging to attempt to blind the investigators overseeing the assessments, as it would rely on the participants not mentioning anything about their intervention.

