### Primary outcome

The effectiveness of WBV will be assessed using the incremental shuttle walk test (ISWT) to examine changes in functional capacity (28). ISWT consists of 12 levels, with a total time signal of 12 minutes. Briefly, participants will be asked to walk on a 10-m long flat walkway following a beeping sound. The walking speed increased by 0.17 meters per second at one-minute intervals, beginning at 0.5 meters per second (level 1) and progressing to a maximum speed of 2.37 meters per second (level 12). The test will be terminated when participants cannot maintain the determined speed or meet the termination criteria following the exercise testing guidelines (29). The primary outcome will be the total distance covered during the test.

It should be noted that if a statistically significant beneficial intervention effect is observed, all patients in the control group will be offered the opportunity to undergo WBV.

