#### Brachial artery flow-mediated dilation (FMD)

The FMD will be performed using a Doppler ultrasound device (Color Doppler ultrasound, Xario 100, Canon Medical Systems). With participants in a supine position, a blood pressure cuff will be positioned around the forearm and an ultrasound probe placed on the same arm proximally to the elbow, and their cardiac cycle will then be measured with a 3-lead electrocardiogram (ECG). A 30-second scan will be recorded as a baseline value prior to cuff inflation. Forearm ischemia will be applied by inflating to a pressure of 250 mmHg for 5 minutes. The cuff will then be deflated, and arterial images will be recorded 15 seconds after deflation and continue for three minutes. The maximum value of arterial diameter will be obtained by the average of 5 consecutive images of cardiac cycle (32). FMD will be calculated using the following equation (33):

$$FMD\;\left(\%\right)=\;\frac{Peak\;diameter-Baseline\;diameter}{Baseline\;diameter}$$

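### The one reason given for not blinding assessors does not cover reading recorded FMD images, and for the 12-week ISWT it supports limiting disclosure, not dropping masking altogether

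*Protocol article*

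**What the plan says.** The Blinding section of the protocol article makes two statements. On participants: "it is not possible to blind participants to the treatment protocol they will be performing". On assessors: "it would be logistically challenging to attempt to blind the investigators overseeing the assessments", and the reason follows directly: "as it would rely on the participants not mentioning anything about their intervention". It makes no exception for any outcome and names no substitute safeguard.

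Three other places bear on this:

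- **Primary outcome.** "The primary outcome will be the total distance covered during the test". On how the test ends: "The test will be terminated when participants cannot maintain the determined speed or meet the termination criteria". The course is 10 m long and the pace is set by beeps.
- **Brachial artery flow-mediated dilation (FMD).** "arterial images will be recorded 15 seconds after deflation and continue for three minutes", and "The maximum value of arterial diameter will be obtained by the average of 5 consecutive images of cardiac cycle".
- **Study design**, on WBV training: "All sessions will be performed under the supervision of an experienced physiotherapist, part of the research team".

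The Figure 1 legend places baseline assessment before randomization. The limitations in the Discussion are the single centre and the absence of angiography; unblinded assessment is not among them.

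**The concern.** A single reason, disclosure by the participant, is used to set masking aside for all assessments. It is a reason about face-to-face contact, and the outcomes differ in how much contact they need. FMD diameters come from recordings that can be measured with nobody else in the room. The ISWT does need contact, but the possibility that some participants will talk does not show that every assessor must know the arm from the start.

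Participants know their treatment, and the primary outcome depends on effort. The assessor is therefore the main remaining place where knowledge of allocation can be limited. An assessor who knows the arm could, without intending to, encourage one group more or judge the end of the test differently. A reader who knows the arm could choose frames or vessel edges differently. Bias of this kind, if it differs between arms, is not reduced by recruiting more participants.

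**Working it through.** The article gives no figure to reproduce on this point, so the check sets the stated reason against each outcome.

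**Does the disclosure argument apply?**

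| Outcome | How it is obtained | Does the reason apply? |
|---|---|---|
| FMD diameter reading | From recorded images, averaging 5 consecutive ones | No. Reading needs no contact with the participant |
| ISWT, 12 weeks | Externally paced, with someone judging failure to keep pace or a termination criterion | In part. Contact is unavoidable, but disclosure can be discouraged and recorded |
| ISWT, baseline | Done before randomization | Not relevant; no allocation exists yet |
| ABI, TBI | ABI by an automated device; TBI measured in the same way at the toe | In part. Contact is needed, but the device limits judgement |
| HbA1c | Blood sample drawn by a medical technologist | Little room for assessor influence |
| SF-36, PAQ | Reported by the participant | Masking the assessor cannot make these blind |

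The stated reason therefore fails outright for FMD reading. For the 12-week ISWT it is real but does not carry the whole conclusion.

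**Who could do it?** A research-team physiotherapist supervises WBV sessions. The supervisor of the treadmill sessions is not identified, and neither is the person who runs the ISWT. The sections on HbA1c and data management mention a medical technologist, a second team member who cross-checks forms, senior investigators and a Data Management Unit. So other people exist, but the article does not say whether any of them is trained or free to run an exercise test. Coding and reading files needs only the existing team.

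**Scale, as illustration only.**

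- ISWT: one length is 10 m, so ending a test one length later adds 10 m to that participant's result. Only a difference in leniency between arms biases the comparison; equal leniency cancels.
- FMD: by the article's formula, the change in FMD is the shift in peak diameter divided by baseline diameter. Assume a baseline of 4.0 mm. A shift of 0.02 mm gives 0.02/4.0 = 0.005, or 0.5 percentage points. Half that shift (0.01 mm) gives 0.25 and twice it (0.04 mm) gives 1.0. The diameter and the shifts are assumptions.
- Type I error: take the 25 evaluable participants per group from the Sample size calculation, a two-sided 0.05 t test, no true difference, and an assumed differential bias of b residual SD. The statistic is noncentral t with 2 × 25 − 2 = 48 degrees of freedom and noncentrality b × √(25/2). The two-sided rejection rate is 5% at b = 0, 6.4% at 0.1, 10.7% at 0.2 and 18.0% at 0.3. If b is instead in raw SD units and the baseline correlation is assumed to be 0.7, the residual SD is √(1 − 0.49) = 0.714. The rates are then 7.7%, 16.3% and 30.7% for b = 0.1, 0.2 and 0.3.

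No value of b can be taken from the article. These figures show how sensitive the test is to a differential bias, not how large that bias is.

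**The case against.** The case for leaving the text alone has four parts.

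First, the article is open about the absence of blinding and gives a reason, and that reason is logistical. For the ISWT this is a trade-off on feasibility and not an error. This largely stands. It is why the proposal for a separate ISWT assessor is conditional on the rota.

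Second, the ISWT is externally paced, with fixed speed steps and guideline termination criteria, which limits the assessor's discretion. This also stands, but some judgement at the end of the test and in encouragement remains.

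Third, a condensed article may leave image-reading detail to a fuller protocol. That is fair as to who reads the images and how. It does not rescue the stated reason, which is printed as the general ground for unmasked assessment and does not fit image reading.

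Fourth, participants' own knowledge of their arm may be the larger threat to an effort-dependent test, and masking assessors does not remove it. That is correct. It limits the gain from masking without removing it.

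A reader might also infer more than the article supports:

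- That blinding is given up, to the trial's harm, for every outcome. The wording is general, but HbA1c, SF-36 and PAQ are not meaningfully affected.
- That someone who knows the arm will select the FMD frames. The article does not say who reads them or with what knowledge.
- That existing staff can certainly run the ISWT. Their availability and training are not stated.

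**Conclusion.** The point holds in a limited form. The disclosure argument does not justify unmasked measurement of recorded FMD images. For the 12-week ISWT it justifies steps to limit disclosure, not giving up masking altogether. The exposure lies in the assessments made after randomization, chiefly the 12-week ISWT (primary) and FMD (secondary). The size of any bias cannot be derived from the article, and the figures above rest on assumed biases, diameters and correlation. The conclusion does not depend on them: it follows from comparing the stated reason with how each outcome is obtained. It assumes only that FMD recordings are kept in a form that can be measured later, which the description of recording makes reasonable.

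**What to change.** In Blinding, keep the statement that participants cannot be blinded and amend the rest:

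1. Store FMD recordings under a code that shows neither arm nor visit, and have the existing team measure diameters from the coded files.
2. Ask participants not to reveal their arm at the 12-week assessment, use a fixed script for the ISWT, and record any disclosure.
3. Where the existing rota allows, have the 12-week ISWT run by a team member who does not supervise training in either arm. Where it does not, add unblinded ISWT assessment to the limitations in the Discussion.

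The cost is file coding and rota planning, with no added visit or procedure. Some unblinding through disclosure will remain, and participants' own knowledge of their arm is unchanged.
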